## Abstract

**Background:**

Type 1 diabetes mellitus (T1DM) in children requires sustained self-management to achieve glycemic targets. Continuous glucose monitoring (CGM) has transformed pediatric diabetes care; yet, adherence to device wear remains inconsistent. In May 2024, Oman launched a national initiative distributing CGMs to children with T1DM across all governorates, creating a real-world opportunity to study adherence determinants and to develop a locally validated AI-assisted predictive tool.

**Objective:**

This multiphase translational research project aims to (1) characterize the population of Omani children with T1DM; (2) identify demographic, psychosocial, dietary, and physical activity correlates of optimal CGM use; (3) develop, train, and validate an AI-assisted behavioral predictive tool “OMNIdiasense” to forecast CGM adherence prior to device dispensing; and (4) pilot test the OMNIdiasense tool.

**Methods:**

Three sequential, interlinked substudies will be conducted. Substudy 1 is a retrospective cohort analysis of routinely collected Al Shifa data for all children who received CGMs between July 2024 and February 2025, with glycemic, anthropometric, and laboratory outcomes compared at baseline and at ≥3 months. Outputs on adherence prevalence, and clinical predictors become the structured input layer for the proposed AI model. Substudy 2 is a cross-sectional, mixed methods study using face-to-face structured interviews with a randomly selected sample of children aged 10-18 years, classified as “CGM optimizers” (≥6 days/week) or “CGM subusers” (<6 days/week or discontinued); responses across validated behavioral, stress, and dietary instruments are compared. Outputs are the psychosocial and behavioral feature set, qualitative themes, and effect sizes that drive feature selection for the AI model. Substudy 3 develops the AI tool (OMNIdiasense), comprising (1) a quasi-experimental single-arm pilot among 100 existing CGM subusers and (2) a parallel pilot randomized controlled trial (n=50; 25 intervention, 25 control) among newly diagnosed children, with assessments at baseline, 3, 6, and 12 months. The primary outcome is between-group difference in CGM adherence; secondary outcomes include hemoglobin A_1c_, anthropometric, cardiovascular, and laboratory measures, and barriers to use. Reporting will follow SPIRIT (Standard Protocol Items: Recommendations for Interventional Trials) 2025 (interventional component), STROBE (Strengthening the Reporting of Observational Studies in Epidemiology; observational component), the CONSORT (Consolidated Standards of Reporting Trials) 2025 extension for pilot and feasibility trials, COREQ (Consolidated Criteria for Reporting Qualitative Research; qualitative component), and TRIPOD+AI (Transparent Reporting of a Multivariable Prediction Model for Individual Prognosis or Diagnosis + Artificial Intelligence; predictive model).

**Results:**

The proposed AI tool is intended as a decision-support adjunct and not a gatekeeping mechanism for CGM access.

**Conclusions:**

To our knowledge, OMNIdiasense is the first AI tool in the Gulf Cooperation Council region to predict pediatric CGM adherence. By targeting behaviorally vulnerable patients before sensor distribution, OMNIdiasense is expected to support clinical benefit and reduce financial waste.

**Trial Registration:**

ISRCTN Registry ISRCTN15827616; https://doi.org/10.1186/ISRCTN15827616

**International Registered Report Identifier (IRRID):**

DERR1-10.2196/99626

## Introduction

### Background and Significance

Type 1 diabetes mellitus (T1DM) one of the most common chronic conditions of childhood, characterized by autoimmune destruction of pancreatic β-cells and a lifelong dependence on exogenous insulin. Despite the documented rise in incidence, epidemiological data on T1DM remain limited in Oman. A single-center study at Sultan Qaboos University Hospital described 144 Omani children with T1DM, of whom 31% presented in diabetic ketoacidosis [1]. A 2-decade review of diabetes epidemiology in Oman documented an increasing prevalence of pediatric T1DM [2]. The only national incidence study, conducted by Soliman and colleagues [3] over 1993-1994, reported incidence rates of 2.45 and 2.62 per 100,000 person-years, with a peak in the 10-14 years age group and seasonal clustering in cooler months. These figures were lower than those reported in Saudi Arabia (27.5 per 100,000 person-years) and Kuwait (15.4 per 100,000 person-years) [4,5]. The Type 1 Diabetes Index estimates that T1DM in Oman is currently growing at approximately 10.2% per year, outpacing the 7.0% growth of type 2 diabetes [6].

In response to this growing burden, His Majesty Sultan Haitham bin Tarik issued a Royal Directive in February 2024 allocating an annual budget for the Ministry of Health (MoH) to provide continuous glucose monitoring (CGM) devices to Omani children with T1DM [7]. The Ministry began nationwide distribution in May 2024 after extensive capacity-building of diabetes-clinic teams in 30 facilities, with approximately 1500 children receiving CGMs by February 2025. CGM technology has evolved markedly since the United States Food and Drug Administration’s first approval in 1999, with modern systems offering real-time interstitial glucose readings, predictive alerts, and integration with insulin delivery [8,9]. However, the well-documented benefits of CGM on hemoglobin A_1c_ (HbA_1c_) reduction, evident in adults with both type 1 and type 2 diabetes, have not been consistently observed in children and adolescents in early meta-analyses [10].

### CGM in Children: Effectiveness, Adherence, and the Adolescent Gap

Pediatric T1DM trajectories vary by age at onset, genetics, and environment. Younger children may experience more aggressive forms of disease with rapid metabolic deregulation [11], and education for both children and caregivers is central to safe self-management as autonomy increases [12]. Long-term complications, including retinopathy, nephropathy, and cardiovascular disease, can begin during youth, and early-onset cohorts demonstrate distinct trajectories of risk [13].

Recent systematic and randomized evidence increasingly supports CGM in pediatric populations: Teo et al [14] confirmed glycemic improvements with CGM use across age strata; Laffel et al [15] demonstrated superiority of CGM over fingerstick monitoring in adolescents and young adults with elevated HbA_1c_; and Hilliard et al [16] showed parental confidence and satisfaction in young children using CGM. Yet, meta-analytic data continue to highlight cost, accessibility, and educational barriers that erode the population-level effect [17,18]. The 2024-2025 update of the International Society for Pediatric and Adolescent Diabetes (ISPAD) Clinical Practice Consensus Guidelines reaffirms that the effectiveness of real-time CGM in children and adolescents is directly related to the amount of sensor wear and that early initiation following diagnosis is associated with better glycemic outcomes [19].

Despite these advances, registry data show that only about 19% of adolescents in the United States T1D Exchange and 46% in the German/Austrian Diabetes Patienten Verlaufsdokumentation registry meet the previous pediatric HbA_1c_ target of <7.5% [20-22], and the targets have since been further tightened to <7.0% [23,24]. Messer et al [25] introduced the operational distinction between “CGM optimizers” (≥6 days/week) and “CGM subusers” (<6 days/week or discontinuation) and demonstrated that perceived benefit and burden of CGM are the strongest psychosocial predictors of consistent adolescent wear. More recent real-world analyses confirm that adherence is independently associated with HbA_1c_ reduction and lower health care use [26], and 2024-2025 work using the “Adherence Starts with Knowledge-12” questionnaire links pubertal stage, diabetes duration, parental involvement, and BMI SD score with low treatment adherence and worse metabolic control [27].

### AI to Predict and Support CGM Adherence

Machine learning and deep learning models trained on wearable and CGM-derived signals are increasingly used to forecast glucose trajectories, detect lifestyle patterns, and personalize care [28-30]. AI-based decision support systems for T1DM have demonstrated feasibility and potential to refine insulin dosing and behavioral guidance [31,32]. A 2024 systematic review identified 8 domains in which AI is reshaping diabetes care, including health monitoring, predictive modeling, lifestyle and dietary management, clinical decision-making, and patient engagement [33]. Personalized blood glucose prediction models combining bidirectional long short-term memory networks with transformer architectures and meta-learning recently achieved clinically acceptable accuracy in pediatric and adult T1DM datasets [34]. To date, however, no AI tool has been developed and validated in the Gulf Cooperation Council region to predict CGM adherence prior to device dispensing in children, and no such tool has been integrated with motivational interviewing (MI)–based behavior change support.

### Study Rationale

The Omani national CGM rollout is pragmatic but resource-intensive, and suboptimal device use risks attenuating both clinical benefit and cost-effectiveness. A locally developed predictive tool, informed by real-world Omani data and culturally adapted psychosocial constructs, could enable risk stratification before CGM dispensing, allowing targeted behavioral support for predicted subusers while reducing waste among children unlikely to engage. This protocol describes a coordinated 3-substudy program to build, validate, and pilot such a tool “OMNIdiasense” in service of His Majesty’s Royal Directive.

### Objectives

The primary objective of this study is to conduct formative research to inform the design of OMNIdiasense, an AI-assisted assessment tool that predicts CGM adherence among Omani children aged 10-18 years with T1DM, and to develop and pilot-test the tool prior to any consideration of national implementation. The study also aims to optimize CGM use through personalized, targeted behavioral interventions for children predicted to be subusers and to estimate the potential cost reduction associated with the implementation of OMNIdiasense. The secondary objectives are to identify the challenges associated with current CGM use among Omani children with T1DM, optimize health care service delivery processes for CGM provision, map the value stream of CGM prescribing and dispensing, identify financial waste related to CGM use through cost analysis, integrate lean management methods into CGM service delivery, and build the capacity of health care workers in the effective use of pediatric CGM technologies.

## Methods

### Overall Study Design and Setting

This is a multiphase, 2-year (2025-2027) translational research project conducted across all 11 governorates of the Sultanate of Oman. The project comprises 3 interlinked substudies: (1) a retrospective cohort study, (2) a cross-sectional mixed methods study, and (3) a pilot evaluation combining a single-arm quasi-experimental design with a parallel pilot randomized controlled trial (RCT). Outputs from substudies 1 and 2 will provide the data and theoretical constructs required to develop the AI-assisted OMNIdiasense tool tested in substudy 3. Figure 1 presents the overall study schematic, and Table 1 summarizes the expected outcomes of each substudy.

**Figure 1 figure1:**
[figure not shown]
Multiphase study flow of the OMNIdiasense project. AUROC: area under the receiver operating characteristic curve; BenCGM: Benefits of Continuous Glucose Monitoring Scale; BP: blood pressure; BurCGM: Burden of Continuous Glucose Monitoring Scale; CGM: continuous glucose monitoring; HbA1c: hemoglobin A1c; HIS: health information system; LFT: liver function test; MoH: Ministry of Health; NN: neural network; PAID: Problem Areas in Diabetes; PAQ-A: Physical Activity Questionnaire for Adolescents; RFT: renal function test; RSQ: Response to Stress Questionnaire;
SEDM: Self-Efficacy for Diabetes Management Scale; SQU: Sultan Qaboos University; SVM: support vector machine; T1DM: type 1 diabetes mellitus; TRIPOD+AI: Transparent Reporting of a Multivariable Prediction Model for Individual Prognosis or Diagnosis + Artificial Intelligence.

**Table 1 table1:** Description of the substudies by design, outcomes, and how each informs the next.

Substudy and aim	Design	Primary outputs/outcomes	How it informs the next phase
Substudy 1: characterize population	Retrospective cohort (Al Shifa records, n~1500)	Population characterization; pre/post HbA_1c_^a^, anthropometrics, BP^b^, lipids, RFT^c^, LFT^d^; sensor-wear days per week; baseline adherence prevalence	Provides the deidentified structured dataset (clinical + adherence label) used as the supervised-learning input for OMNIdiasense; defines candidate clinical predictors.
Substudy 2: identify correlates	Cross-sectional mixed methods (n=240 face-to-face interviews + qualitative open-ended responses)	Quantitative effect sizes for BenCGM^e^, BurCGM^f^, RSQ^g^, SEDM^h^, PAID-Peds^i^, PAQ-A^j^, and dietary screener on optimizer vs subuser status; qualitative themes on barriers and facilitators	Provides the psychosocial and behavioral feature set, the qualitative themes that inform MI content, and the effect sizes used to prioritize features for the AI model.
Substudy 3: AI tool development (7-step pipeline with validation hierarchy)	Prediction model development on combined substudy 1 + 2 dataset	OMNIdiasense risk score (probability of subuser status), with discrimination, calibration, and fairness metrics	The validated model becomes the assessment tool tested in the 2 evaluation arms below.
Substudy 3: quasi-experimental single-arm pilot	Quasi-experimental, n=100 existing subusers	Within-person change in adherence and HbA_1c_ after OMNIdiasense-guided MI sessions	Feasibility, acceptability, and effect-size estimates for a future definitive trial.
Substudy 3: pilot RCT^k^ with appropriate reporting standards	Parallel 1:1, n=50 newly diagnosed (25 intervention, 25 control)	Between-group difference in CGM^l^ adherence at 12 months; secondary clinical, behavioral, and satisfaction outcomes	Generates the effect-size, recruitment, retention, and fidelity estimates required for a definitive multicenter trial.

^a^HbA_1c_: hemoglobin A_1c_.

^b^BP: blood pressure.

^c^RFT: renal function test.

^d^LFT: liver function test.

^e^BenCGM: Benefits of Continuous Glucose Monitoring Scale.

^f^BurCGM: Burden of Continuous Glucose Monitoring Scale.

^g^RSQ: Response to Stress Questionnaire.

^h^SEDM: Self-Efficacy for Diabetes Management Scale.

^i^PAID-Peds: Problem Areas in Diabetes-Pediatric version.

^j^PAQ-A: Physical Activity Questionnaire for Adolescents.

^k^RCT: randomized controlled trial.

^l^CGM: continuous glucose monitoring.

CGM distribution in Oman commenced in May 2024 following extensive capacity-building of diabetes clinic staff in 30 health facilities across all governorates. By February 2025, approximately 1500 children with T1DM had received CGMs, recorded centrally in the national Al Shifa health information system.

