#### AI Model Development (OMNIdiasense)

The AI tool will be codeveloped by the MoH digital-health team and computer scientists from Sultan Qaboos University. The development pipeline comprises 7 steps, expanded below to address missing data, class imbalance, overfitting, feature selection, calibration, fairness, and external validation.

Data preparation: integration and cleaning of deidentified data from substudies 1 and 2 (demographic, clinical, laboratory, anthropometric, psychosocial, and behavioral).Feature engineering: selection of candidate predictors informed by substudy 2 effect sizes and clinical face validity.Model selection and training: comparison of supervised classifiers (logistic regression, gradient-boosted trees, support vector machines, and a small feed-forward neural network) using stratified cross-validation; evaluation by area under the receiver operating characteristic curve, sensitivity, specificity, calibration, and net reclassification improvement.Behavioral pattern recognition: unsupervised clustering of lifestyle and dietary data to derive interpretable phenotypes used for personalized recommendations.Initial testing: internal validation on a held-out 20% partition.Optimization: iterative refinement on the basis of clinician and family feedback.Deployment: secure web-based interface integrated into the diabetes clinic workflow with role-based access and audit logging.

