#### External Validation

Internal validation alone is insufficient before clinical use. The validation plan therefore includes three layers: (1) internal validation on the held-out 20% partition, (2) temporal validation on a prospectively collected cohort enrolled at least 3 months after model lock, and (3) a preplanned external multisite replication in 2 Gulf neighboring sites (institutions to be confirmed at the start of the pilot phase) using the same data-collection forms and the same outcome definitions. Until external validation is satisfactory, OMNIdiasense outputs will be presented to clinicians as decision support only and will not influence CGM allocation (see the Ethical Considerations section).

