## Results

The project was funded in March 2025 by the Ministry of Higher Education, Research and Innovation through the Strategic Research Program, supervised by the National Health Research Center (agreement number RIA/SRP/MoH/25/01; Multimedia Appendix 6). Ethical approval was issued in November 2024 (MoH/CSR/24/29506), and the trial was prospectively registered with ISRCTN on April 22, 2025 (ISRCTN15827616) (Multimedia Appendix 12). Data extraction from Al Shifa for substudy 1 began in March 2025; as of April 2026, baseline records for the recruited sample have been compiled, and cleaning and pre-post comparative analyses are underway. Substudy 2 interview tools have been prepiloted in Muscat with 15 adolescents in February 2026, and full recruitment is planned to begin in June 2026. AI model prototyping with synthetic data and feature engineering using substudy 1 outputs is scheduled for the third quarter of 2026; substudy 3 pilot recruitment is planned for the fourth quarter of 2026, with the final 12-month follow-up expected to conclude by the end of 2028. Findings from substudies 1 and 2 are anticipated for publication in mid-2027, the OMNIdiasense development paper, and the pilot evaluation results in late 2027.

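### Table 1 sends a validated model into the pilot, but the schedule allows at most internal validation by then, and neither the held-out test nor the RCT score outcomes are tied to one locked version

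*Protocol article*

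**What the plan says.** Table 1, in the row on AI tool development, gives the design as "Prediction model development on combined substudy 1 + 2 dataset", refers to a validation hierarchy, and concludes: "The validated model becomes the assessment tool tested in the 2 evaluation arms below".

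External Validation sets out that hierarchy: (1) internal validation on the held-out 20%, (2) "temporal validation on a prospectively collected cohort enrolled at least 3 months after model lock", and (3) replication at two neighboring Gulf sites. It regards the internal layer as not enough for clinical use. It also foresees use before external validation is satisfactory, as decision support with no bearing on who gets a CGM.

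The Results section gives the dates. For substudy 2, "full recruitment is planned to begin in June 2026". Then, "AI model prototyping with synthetic data and feature engineering using substudy 1 outputs is scheduled for the third quarter of 2026". Finally, "substudy 3 pilot recruitment is planned for the fourth quarter of 2026". No lock date appears, and no section says which validation layer must be passed before the first pilot child.

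AI Model Development lists seven steps. Step 5 is the held-out test, step 6 is "Optimization: iterative refinement on the basis of clinician and family feedback", and step 7 is deployment. Bias Monitoring During the Pilot provides for DMC review of subgroup performance every 6 months. If a disparity is found, outputs for that subgroup are paused while the model is recalibrated. Outcomes lists change in the risk score as a secondary outcome. Table 2 names the score as the source for optimizer or subuser status, under the primary outcome, at all four visits.

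**The concern.** Three things need to agree: the label Table 1 puts on the model, the validation layers the protocol defines, and the calendar. They do not. A reader of Table 1 would take the tool to have passed the stated hierarchy, when at pilot start it can have passed the first layer at most.

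The second issue is which version the numbers describe. The pilot is meant to supply effect-size and fidelity estimates for a definitive trial, and the score is fed back to families in the motivational-interviewing sessions. If the held-out performance comes from a version before refinement, or if scores at different visits come from different calibrations, neither the performance figure nor the change in score refers to one defined tool. With 25 children in the intervention arm, a mixture of versions would be hard to separate afterwards.

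**Working it through.** **Inputs**
- Prototyping: third quarter of 2026, 1 July to 30 September (Results).
- Pilot recruitment opens: fourth quarter of 2026, 1 October to 31 December (Results).
- Gap from lock to temporal-cohort enrollment: at least 3 months (External Validation).
- Time to observe adherence in that cohort: not stated. I assume 3 months, the minimum exposure window of substudy 1 (Substudy 1, Design and Population), and also show 12 months.
- Lock date: not stated. I take any date in the prototyping quarter.

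**Timing.** First temporal result = lock + 3 months + label window. This allows no time for accruing the cohort or analyzing it.

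| Lock | Temporal cohort can start | First 3-month labels | First 12-month labels |
|---|---|---|---|
| 1 Jul 2026 | 1 Oct 2026 | 1 Jan 2027 | 1 Oct 2027 |
| 15 Aug 2026 | 15 Nov 2026 | 15 Feb 2027 | 15 Nov 2027 |
| 30 Sep 2026 | 30 Dec 2026 | 30 Mar 2027 | 30 Dec 2027 |

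Lag behind the opening of recruitment, with the 3-month label:
- Smallest: lock 1 July, recruitment opens 31 December. 1 Jan 2027 − 31 Dec 2026 = 1 day.
- Largest: lock 30 September, recruitment opens 1 October. 30 Mar 2027 − 1 Oct 2026 = 180 days, about 6 months.

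In reverse, a temporal result in hand at the start requires lock = start − 6 months. That is 1 April 2026 for a 1 October start and 30 June 2026 for a 31 December start. Both precede the prototyping quarter.

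**Sensitivity to the label.** From the earliest lock (1 July) to the latest start (31 December) is just under 6 months, of which 3 are the required gap. A temporal result before the pilot therefore needs a label shorter than 3 months, the earliest lock, the latest start and almost no accrual or analysis time. A lock on 1 July is itself unlikely, because the substudy 2 interviews that feed the model begin recruiting only in June 2026. A lock after 30 September moves the result later month for month.

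**Order of steps.** The held-out test is step 5 and refinement is step 6. If step 6 changes coefficients, features, calibration or thresholds, the model deployed at step 7 is not the one tested. Testing again on the same 20% after each refinement would use up its independence.

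**Effect of recalibration on the score outcomes.** Let s1 and s2 be the score before and after recalibration, and x0 and x12 a child's predictors at baseline and 12 months. The recorded change is

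s2(x12) − s1(x0) = [s2(x12) − s1(x12)] + [s1(x12) − s1(x0)].

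The first bracket is purely a version effect. For a child whose predictors do not change, the second bracket is zero and the whole recorded change is the version effect. The same applies to a child who crosses the optimizer/subuser cut-off in Table 2. If both RCT arms were rescored at the same time, the shift would fall partly on both, so the between-arm bias need not equal the full bracket. Each child's 12-month follow-up spans two DMC review intervals (12 / 6 = 2), so the clause can apply within a child's own series of scores.

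**The case against.** The strongest reply is that this is a pilot of a research-stage tool, not the clinical use that the protocol guards against. No section makes temporal validation a condition for the pilot. External Validation expects decision-support use before external validation is satisfactory. How the OMNIdiasense Score Will Be Used keeps the score away from CGM access and out of the clinical record, and families are told that the score is a research-stage estimate. All of that stands. A reader might infer from the dates that children will receive an unvalidated tool. The documents do not support this: nested cross-validation and the held-out test are planned ahead of deployment. The supportable statement is at most internally validated. The 80/20 split is to be made in time order where possible, but the protocol still classes it as the internal layer.

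A reader might also infer that the tool will change during the RCT. Step 6 precedes deployment, so it does not show that. It may also partly concern the interface, since Patient and Public Involvement places family input in interface refinement. Only the recalibration clause allows change during the pilot. It is conditional on a detected disparity, involves the DMC and is logged for the results paper.

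Nor do the dates support a lag of at least 3 months. That would follow only from treating 30 September as the earliest lock, when it is the last day of the prototyping quarter.

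Version control might be set out in a fuller document. That does not cover what this article itself states: the label in Table 1, the order of steps 5 and 6, and the use of the score as an outcome.

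**Conclusion.** The point holds in a limited form. The first pilot children can receive at most an internally validated tool, which Table 1 calls validated without qualification. First temporal results come about 0 to 6 months after recruitment opens, assuming a lock in the third quarter of 2026 and a 3-month label. A later lock, a longer label or any accrual time extends the lag. The final follow-up is due by the end of 2028, so enrollment may run to about the end of 2027, and later participants could be scored by a model that has temporal results.

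Two consequences are conditional. The reported held-out performance is misattributed only if step 6 alters the fitted model. The score outcomes are distorted only if the recalibration clause is used. The primary measure in the Outcomes text, mean wear days per week, is not computed from the score and is not exposed to that distortion; the score-based status in Table 2 and the secondary change in score are. The documents do not allow the size of either effect to be estimated.

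**What to change.** 1. In Table 1, write internally validated, and state in External Validation which layer must be complete before the first pilot child.
2. Run the held-out 20% test once, after any refinement that touches the model, on the version that is then locked. Lock it before the first RCT randomization and give the version identifier.
3. Keep the fairness safeguard as it is. Compute every RCT score outcome (the change in score and the score-based status in Table 2) with the locked version for all children and visits, and report by version which participants received recalibrated outputs.

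The cost is rescoring stored predictor data with the locked model, one extra table by version, and possibly a short delay to the planned start in the fourth quarter of 2026 if refinement has to finish before the held-out test. Recalibrated outputs can still reach families under the existing safeguard; they simply do not enter the outcome calculation.
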